## **13. ADVERSE AND SERIOUS ADVERSE EVENTS**

### **13.1. Definition of Adverse Events (AE)**

An AE is any untoward medical occurrence associated with the use of an investigational product in humans, whether or not considered product related. An AE can therefore be any unfavorable and unintended sign (including an abnormal laboratory finding), symptom, or disease temporally associated with the use of an investigational product, whether or not considered related to the investigational product. Pre-existing events that increase in frequency or severity in nature during or as a consequence of use of an investigational product in human clinical trials will also be considered as AEs. Any medical condition or clinically significant laboratory abnormality with an onset date before the first date of study product administration is considered to be pre-existing, and should be documented in the source document for the participant.

All AEs starting with Visit 3 before treatment, during treatment, or by the time of the follow-up call one to two weeks after the last study visit, whether or not they are related to the study, must be recorded on forms provided by CONRAD.

According to 21 CFR 312.32 “IND Safety Reports” the following definitions of terms apply to AEs occurring in clinical studies involving drugs.

#### **13.1.1. Suspected Adverse Reaction**

A suspected adverse reaction is “any AE for which there is a reasonable possibility that the study product caused the event.” An AE is considered to be a suspected adverse reaction only if there is evidence to suggest a causal relationship between the study product and the AE. Examples include:

- A single occurrence of an event that is uncommon and known to be strongly associated with product exposure (Examples, not necessarily applicable to this study include angioedema, hepatic injury, Stevens-Johnson Syndrome)
- One or more occurrences of an event that is not commonly associated with product exposure, but is otherwise uncommon in the population exposed to the study product (e.g., tendon rupture)
- An aggregate analysis of specific events observed in a clinical trial (such as known consequences of the underlying disease or condition under investigation or other events that commonly occur in the study population independent of product exposure)

#### **13.1.2. Adverse Reaction**

An adverse reaction is any AE caused by the study product. Adverse reactions are a *subset* of suspected adverse reactions.

#### **13.1.3. Serious Adverse Event (SAE) or Serious Suspected Adverse Reaction**

An AE or suspected adverse reaction is considered “serious” if, in the view of either the investigator or the sponsor, it:

- Results in death;

- Is immediately life-threatening;
- Requires in-patient hospitalization or prolongation of existing hospitalization;
- Results in persistent or significant disability or incapacity;
- Results in a congenital abnormality or birth defect; or
- Is an important medical event that may jeopardize the patient or may require medical or surgical intervention to prevent one of the outcomes listed above.

All SAEs starting with Visit 3, before treatment, during treatment, or by the time of the follow-up call/contact one to two weeks after the last study visit, whether or not they are related to the study, must be recorded on forms provided by CONRAD.

#### **13.1.4. Unexpected Adverse Event or Unexpected Suspected Adverse Reaction**

An AE or suspected adverse reaction is considered “unexpected” if it is not listed in the investigator brochure or is not listed at the specificity or severity that has been observed; or, if an investigator brochure is not required or available, is not consistent with the risk information described in the general investigational plan or elsewhere in the current application, as amended. For example (not necessarily applicable to this study), under this definition, hepatic necrosis would be unexpected (by virtue of greater severity) if the investigator brochure referred only to elevated hepatic enzymes or hepatitis. Similarly, cerebral thromboembolism and cerebral vasculitis would be unexpected (by virtue of greater specificity) if the investigator brochure listed only cerebral vascular accidents. “Unexpected,” as used in this definition, also refers to AEs or suspected adverse reactions that are mentioned in the investigator brochure as occurring with a class of drugs or as anticipated from the pharmacological properties of the drug, but are not specifically mentioned as occurring with the particular drug under investigation.

### **13.2. Relationship to Study Drug**

An Investigator who is qualified in medicine must make the determination of relationship to the investigational product for each AE. The Investigator should decide whether, in his or her medical judgment, there is a reasonable possibility that the event may have been caused by the investigational product. For each AE, the assessment of relatedness should be made using the following scale:

- Unrelated: Onset of the AE had no reasonable temporal relationship to administration of the study product or a causal relationship to administration of the study product is biologically implausible or the event is attributed to an alternative etiology.
- Possibly Related: Onset of the AE has a reasonable temporal relationship to study product administration and a causal relationship is not biologically implausible.
- Probably Related: Onset of the AE has a strong temporal relationship to administration of the study product that cannot be explained by the participant’s clinical state and a causal relationship is not biologically implausible.
- Definitely Related: Onset of the AE shows a distinct temporal relationship to administration of the study product that cannot be explained by the participant’s clinical state or other factors or the AE occurs on rechallenge or the AE is a known reaction to the product or chemical group or can be predicted by the product’s pharmacology.

If the relationship between the AE/SAE and the investigational product is determined to be “possible,” “probable,” or “definite” the event will be considered to be related to the investigational product for the purposes of expedited regulatory reporting.

### 13.3. Recording and Grading Adverse Events for Severity

Adverse events spontaneously reported by the participant and/or in response to an open question from the study personnel or revealed by observation will be recorded during the study at the investigational site. The AE term should be reported in standard medical terminology when possible. For each AE, the investigator will evaluate and report the date of onset, date of resolution, intensity, causality, action taken, serious outcome (if applicable), and whether or not it caused the patient to discontinue the study. Each AE will be graded for severity using the August 2009 update of the DAIDS Table for Grading the Severity of Adverse Events which can be found at <http://rsc.tech-res.com/safetyandpharmacovigilance/>.

**Figure 2: Grading the Severity of Adverse Events**

|                         |                                                                                                                                                                                                                                                                              |
|-------------------------|------------------------------------------------------------------------------------------------------------------------------------------------------------------------------------------------------------------------------------------------------------------------------|
| Adult and Pediatric AEs | http://rsc.tech-res.com/Document/safetyandpharmacovigilance/
Table_for_Grading_Severity_of_Adult_Pediatric_Adverse_Events.pdf |
| Female Genital AEs      | http://rsc.tech-res.com/Document/safetyandpharmacovigilance/
Addendum_1_Female_Genital_Grading_Table_v1_Nov_2007.pdf                   |

For clinical AEs NOT identified in the DAIDS AE Grading Tables, the following scale (as listed in the DAIDS Table for Grading the Severity of Adult and Pediatric AEs) should be used to grade severity:

- Mild: Symptoms causing no or minimal interference with usual social and functional activities
- Moderate: Symptoms causing greater than minimal interference with usual social and functional activities
- Severe: Symptoms causing inability to perform usual social and functional activities
- Potentially Life-Threatening: Symptoms causing inability to perform basic self-care functions OR medical or operative intervention indicated to prevent permanent impairment, persistent disability, or death

It is important to distinguish between serious and severe AEs. Severity is a measure of intensity whereas seriousness is defined by the criteria under Section 13.1.3. An AE of severe intensity may not necessarily be considered serious.

Colposcopic findings should be reported on colposcopic finding CRFs and should not be reported as AEs on AE CRFs. Colposcopic findings are defined as severe when they involve deep disruption of the epithelium. An area of the epithelium with bleeding should be considered deeply disrupted. Severe colposcopic findings possibly, probably, or definitely related to product use must be immediately reported to CONRAD within 24 hours of discovery. In addition, a completed colposcopic finding CRF must be faxed or emailed to CONRAD as soon as possible.

Should a pregnancy occur, it must be reported as soon as possible to CONRAD and recorded on CONRAD’s pregnancy CRF. The participant will be discontinued from the study and appropriate exit procedures will be followed (Section 8.3.3). Note that pregnancy in itself is not regarded as an AE unless there is a suspicion that an investigational product may have interfered with the effectiveness of a contraceptive medication. If the participant has been exposed to study product, the course of the

pregnancy should be followed until it has an outcome (spontaneous miscarriage, elective termination, normal birth or congenital abnormality). If a pregnancy is diagnosed, study product to which the participant has been assigned may be unblinded. If the participant seeks care outside the site, every effort should be made to obtain her consent for the site to receive a copy of her medical records related to the pregnancy, its outcome and the health of the neonate, if applicable.

Reports of congenital abnormalities/birth defects are SAEs. Spontaneous miscarriages should be reported and handled as AEs. Elective abortions without complications should not be reported as AEs.

### **13.4. Reporting Serious Adverse Events**

All SAEs whether or not considered a suspected drug reaction will be recorded starting with Visit 3, before treatment, during treatment, or by the time of the follow-up call/contact one to two weeks after the last study visit.

Any SAE including those listed in the protocol or investigator brochure must be reported to CONRAD within 24 hours of discovery. If there is any question whether the event meets the criteria for “serious” it should be reported anyway. In addition, a completed SAE Form must be faxed or emailed to CONRAD as soon as possible. The Investigator must complete, sign and date the SAE pages, verifying the accuracy of the information recorded on the SAE pages with the corresponding source documents.

Additional follow-up information, if required or available, should all be faxed to CONRAD within one business day of receipt and this should be completed on a follow-up SAE form and placed with the original SAE information and kept with the appropriate section of the CRF and/or study file.

CONRAD will notify the U.S. Food and Drug Administration (FDA) and all participating investigators (i.e., all investigators to whom CONRAD is providing the relevant drug under its IND(s) or under any investigator's IND) in an IND safety report of potentially serious risks, from clinical trials or any other source, as soon as possible, but in no case later than 15 calendar days after CONRAD determines that the information qualifies for reporting under CFR 312.32(c)(1) which includes serious and unexpected suspected adverse reactions, findings from other studies, findings from animal or in-vitro testing, and increased rates of occurrences of serious suspected adverse reactions. In each IND safety report, CONRAD will identify all IND safety reports previously submitted to FDA concerning a similar suspected adverse reaction, and will analyze the significance of the suspected adverse reaction in light of previous, similar reports or any other relevant information.

CONRAD will notify the FDA of any unexpected fatal or life-threatening suspected adverse reactions as soon as possible, but in no case later than 7 calendar days after CONRAD initially receives the information.

CONRAD will promptly investigate and follow up on all safety information it receives, with the cooperation of the investigator. Follow-up information relevant to an IND safety report will be submitted as soon as the information is available and will be identified as such, i.e., “Follow-up IND Safety Report.”

The investigator is responsible for complying with IRB requirements for AE reporting and supplying CONRAD with copies of such correspondence

The blind may be broken for serious or unexpected AEs if knowledge of the treatment received is necessary for interpreting the event, may be essential for the medical management of the participant, or may provide critical safety information about a drug that could have implications for the ongoing conduct

of the trial (e.g., monitoring, informed consent). In general, if the blind is broken and the participant was receiving placebo, the event should not be reported in an IND safety report because there is not a reasonable possibility that the drug caused the AE. If the blind is broken and the subject was receiving the study drug, the suspected adverse reaction must be reported in an IND safety report.

### **13.5. Temporary Product Hold/Permanent Discontinuation in Response to Adverse Events**

All AEs are defined by the Division of AIDS Table for Grading the Severity of Adult and Pediatric Adverse Events, Version 1.0, December 2004 (Clarification dated August 2009), and Addendum 1, Female Genital Table for Use in Microbicide Studies and Addendum 3, Rectal Grading Table for Use in Microbicide Studies (Clarification dated May 2012).

#### **13.5.1. Grade 1 or 2**

In general, a participant who develops a Grade 1 or 2 AE regardless of relationship to study product that is not specifically addressed below may continue product use. If the PI opts to temporarily hold study product, CONRAD must be notified.

Follow-up testing for Grade 2 laboratory test results should be performed at scheduled study visits, at a minimum, until resolution or stabilization has been documented. More frequent testing may be performed at any time if required to properly monitor and/or manage participant safety, at the discretion of the PI/designee.

#### **13.5.2. Grade 3 and 4**

A participant who develops a Grade 3 or a Grade 4 AE that is either urogenital or product-related should have the product temporarily withheld, in consultation with CONRAD. If a participant develops a Grade 3 or Grade 4 AE that is not urogenital or product-related, the PI/designee must contact CONRAD prior to temporarily withholding product. In either case, the PI/designee must continue the temporary product hold until a recommendation is obtained from CONRAD. If, in consultation with CONRAD, product use is resumed and the same AE recurs at the same grade level at any time during the study, study product must then be permanently discontinued.

## **14. STATISTICS**

### **14.1. Sample Size Justification**

Sample size for this Phase I study is based on feasibility considerations (e.g., cost and time) and not on statistical criteria.

### **14.2. Analysis Plan**

An expanded SAP will be written and approved before scheduled unblinding following data base lock. Any decisions regarding data handling, exclusions from analysis, etc. made subsequent to the approval of this protocol will be documented in the SAP or final study report. Decisions, if any, made by unblinded personnel will be noted.

### **14.3. General Statistical Issues**

*Evaluation of Study Objectives:* Study objectives will be evaluated by clinical review of descriptive summaries and graphical displays. To supplement clinical judgments, comparisons on selected continuous endpoints between each active group vs. placebo may be estimated from statistical models, with terms for treatment and center as fixed effects and time of measurement as a repeated measure. Comparisons may also be made between the TFV/LNG-ring group vs. the TFV-alone ring group. Estimates and 95% confidence intervals will be provided. It is acknowledged that the trial is not necessarily powered to test hypotheses regarding group differences. Further details on modeling strategy and specifications will be described in the SAP.

Some of the endpoints may require new assay methods in order to obtain meaningful measurements. It is possible that assays for some of the planned endpoints may not be run or that the results may not be statistically analyzed if lab personnel or the CONRAD Study Clinician feel that the measurements are not reliable. These decisions will be made and documented prior to unblinding.

*Descriptive Statistics:* Categorical variables will be summarized by frequencies and percentages. Continuous variables will be summarized by means, standard deviations, medians, interquartile ranges, minima and maxima. Some PK measurements (e.g., serum concentrations) may fall below the analytic limit of detection and therefore be imputed, if possible, or censored. Summary statistics that include censored observations will be evaluated from medians and other percentiles of the distribution, as censored data can contribute to percentiles of the distributions but not to means and standard deviations.

*Imputation:* Concentrations that are detectable but below the lower limit of quantification (LLOQ) will be set to one-half the value LLOQ if LLOQ is defined; concentrations below the limit of detection will be set to 0, if limit of detection is defined. Otherwise, no imputation is anticipated. If needed, rules for imputing missing values will be created and will be documented in the analysis plan or statistical report.

*Control of Type I Error:* This Phase I study is descriptive in nature. P-values and confidence intervals around estimates of treatment differences will not be adjusted for multiple analyses. These statistics are provided to guide clinical judgment; inferences based on statistical significance (or lack thereof) should be made cautiously.

*Controlling for Center and Evaluating Center Differences:* Baseline socio-demographic statistics, study disposition (completion; reasons for early discontinuation), and descriptive statistics for a few selected key endpoints (to be identified in the SAP) will be computed separately by center to allow review of center differences. Statistical tests will stratify on center when possible.

*Definition of Baseline:* Baseline is defined as the non-missing measurement obtained closest to but prior to randomization and first insertion of ring at Visit 4.

*Subject-Specific Listings:* Tables and graphs will be accompanied by subject-specific listings of data as needed.

*Classification of Sampling Time Point:* Sampling time point will be based on actual time (i.e., allocation errors are ignored). Sampling times within windows if defined in the study manual or SAP will be considered to have occurred at the assigned time. Modifications (e.g., creation of new time points) may be made based on blinded review of actual sampling times and documented in the SAP or statistical report. Samples that fall out of these classifications will not be included in summary statistics based on sampling time point but will be included in other analyses.

#### **14.4. Analysis Populations**

A flowchart showing the number of participants screened, enrolled, randomized, completed, contributing to each analysis population, etc. will be reported in accordance with CONSORT guidelines.

The Enrolled Population consists of all participants who undergo genital sampling at Visit 3 whether or not they are randomized or use a study IVR. Reasons why an enrolled participant was not randomized or did not use a study IVR will be listed.

The RP consists of all participants who were randomized and inserted the study IVR at Visit 4. Treatment groups are defined on the basis of treatment assigned. (Allocation errors are ignored.) This will be the primary analysis population for baseline characteristics and study disposition.

The TP is the subset of RP who provided at least some post-insertion safety, PK, or PD data. Treatment groups are defined by treatment received. The TP will be the primary analysis population for all remaining objectives unless TP and RP are identical, in which case the analysis population will be identified as the RP.

The Completer Population is the subset of TP who are considered adherent based on the definition in Section 15.2, and completed the study i.e. provided all key data as defined in the SAP. Some descriptive statistics and graphical displays e.g., concentration data may be repeated on the Completer Population to evaluate data within consistent groups. This will be addressed further in the SAP.

Additional populations or refinements to these definitions, if needed due to unanticipated circumstances, will be described in the SAP or statistical report.

#### **14.5. Interim Analysis**

An interim analysis may be conducted after at least 15 participants (both sites combined) have completed the study. The interim analysis is intended to evaluate drug-release parameters to help inform the direction of product development and will consist of descriptive statistics and graphical displays of drug concentrations by treatment group and sampling time point or other descriptive analysis as described in the SAP. While the lead statistician will design the analysis, the analysis will be carried out and verified

by FHI 360 statisticians not otherwise involved in the study (other than, perhaps, as the unblinded randomization statistician). Results for individual participants will not be identified by participant number. Grouped results will not be identified by type of IVR but by “Group A,” “Group B,” etc. It is acknowledged that the nature of the results (e.g., non-zero values) can unblind reviewers to the identity of these groups. Results will be sent via password-protected secure file server to the Director of CONRAD’s Product Development Department or other authorized individual. Recipients of the interim statistical report at CONRAD will maintain appropriate security and confidentiality, and will share the results with other CONRAD staff only on a need-to-know basis. Communication of results with CONRAD staff directly involved in this study will be documented (e.g., who, when, level of detail) and implications, if any, for interpretation of results will be discussed in the clinical study report.

## **14.6. Evaluation of Primary Objectives**

### **Genital and Systemic Safety**

Only treatment-emergent AEs, defined as an AE with onset on or after insertion of IVR, will be included in the analysis; AEs reported on CRFs with onset prior to insertion will be listed. AEs will be summarized separately by treatment group based on MedDRA Preferred Term and System/Organ Class. The number of subjects reporting at least one episode of a given AE category (Preferred Term) as well as number of episodes will be summarized and listed. SAEs, if any, will be identified.

Other than AEs, genital safety endpoints will be summarized separately by treatment group and time of measurement.

Treatment effects on serum chemistries, lipids, CBC, pH, and Nugent score will be evaluated clinically from shift tables reflecting change from baseline based on categories to be developed by the CONRAD Study Clinician and described in the SAP (e.g. Normal→ Abnormal/High [e.g., serum chemistries, lipids, or CBC; Normal→ Intermediate → BV [Nugent score]). Shift tables will be created for each follow-up visit at which measurements were obtained. In addition, changes in pelvic examination results immediately before vs. immediately after IVR insertion at Visit 4 will be listed.

Changes in soluble markers of innate mucosal immunity and inflammatory response in CVL, HIV-1 target immune cell phenotypes and activation/proliferation markers, and cervicovaginal epithelial histology will be evaluated clinically from descriptive statistics by treatment group and time point and supplementary graphical displays (e.g., box-plots). Statistical models comparing treatment groups on these endpoints may be addressed in the SAP.

Separate box-plots for immune markers measured in the presence of semen (as determined by the semen biomarkers) vs. those from the same treatment group and sampling time point without the presence of semen will be created, if necessary, to assist with interpretation of these markers.

Non-iatrogenic colposcopy findings will be described based on characteristics at the first observation, though characteristics at all observations will be listed. Development of ulcerations, abrasions, edema, and other findings will be based on diagnoses made by site colposcopists.

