- Moderate to severe urogenital symptoms (e.g., genital burning, irritation, stinging, pressure, rash, itching, discharge, odor, urgency, dysuria, or hematuria)
- Pelvic/lower abdominal pain
- Moderate to heavy intermenstrual bleeding (more than she would have during a normal period) or, during the week following a biopsy, any bleeding more than spotting

She will be asked to come in for an evaluation, if indicated.

- The participant will be reminded of the restrictions on vaginal activity (including intercourse) and product use as described at Visit 2.

Visit 4 will take place on day 7 (+/- 1 day) of one of the first two menstrual cycles after Visit 3, ideally in the first menstrual cycle.

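### Treatment-emergent AEs are defined by onset alone and colposcopic findings are described as first seen, so the primary safety summaries can miss worsening with the ring in place

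*Protocol*

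**What the plan says.** **AEs.** Section 14.6 limits the primary AE analysis by onset date: "Only treatment-emergent AEs, defined as an AE with onset on or after insertion of IVR, will be included in the analysis". Earlier events are set aside: "AEs reported on CRFs with onset prior to insertion will be listed". The synopsis gives the same onset-only definition. Section 13.1 takes a wider view of what an AE is and includes "Pre-existing events that increase in frequency or severity in nature during or as a consequence of use of an investigational product". It also opens the recording window before any product is used: "All AEs starting with Visit 3 before treatment, during treatment, or by the time of the follow-up call".

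**Colposcopy.** Section 14.6 states: "Non-iatrogenic colposcopy findings will be described based on characteristics at the first observation, though characteristics at all observations will be listed". Section 13.3 sets the severity criterion: "Colposcopic findings are defined as severe when they involve deep disruption of the epithelium". The same section directs colposcopic findings to their own form and keeps them off the AE form.

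**Related text.** Section 14.6 promises that genital safety endpoints other than AEs will be summarised by arm and time of measurement. It assigns shift tables to chemistries, lipids, CBC, pH and Nugent score. The synopsis promises shift tables from baseline in more general terms.

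**The concern.** The protocol treats worsening under product as an AE in one section and selects events for the primary analysis by onset alone in another. An event that begins after the Visit 3 biopsies and increases in grade with the ring in place satisfies section 13.1. Under section 14.6 it may only be listed.

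The colposcopy rule points the same way. A finding that heals may be described near its worst, and a finding that progresses is described at its mildest.

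Local toxicity that builds up during use is a central question for a Phase I ring study. Section 14.3 says objectives are judged by clinical review of descriptive summaries and graphs. If the arm-level summaries do not carry progression, that review starts from an incomplete picture.

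**Working it through.** No stated figure needs reproducing, because section 14.1 bases the sample size on feasibility. The check is a comparison of texts, followed by a note on scale.

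**1. Is there a pre-insertion window?** Yes. Recording starts at Visit 3. Section 9.3 takes one cervicovaginal biopsy at the Dominican Republic site. At EVMS it takes three cervicovaginal biopsies and one endometrial biopsy. Then "Visit 4 will take place on day 7 (+/- 1 day) of one of the first two menstrual cycles after Visit 3". Counting from nominal cycle day 24 (Table 4) to day 7, with the 26 to 35 day cycles of section 8.1:
- first cycle: (26 − 24) + 7 = 9 days, to (35 − 24) + 7 = 18 days
- second cycle: 9 + 26 = 35 days, to 18 + 35 = 53 days

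Genital events with onset before insertion are therefore foreseeable, although a longer gap leaves more time for them to resolve.

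**2. Does any text bring a worsening into the AE table?**

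| Source | What it fixes | What it leaves open |
|---|---|---|
| 13.1 | Worsening of a pre-existing event is an AE | Whether it gets a new record and its own onset date |
| 13.3 | Onset date, resolution date and intensity are reported for each AE | How a change of grade within an event is recorded |
| 14.6 and synopsis | Onset on or after insertion enters; earlier onset is listed | Worsening of an event with earlier onset |

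If the site opens a new record, the worsening has a post-insertion onset and is counted. If the site updates the old record, the onset stays before insertion and the event is only listed. The text directs neither course, so sites may differ.

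**3. Can a colposcopic finding progress outside the summary?** Table 11 schedules colposcopy at Visit 4 before insertion and at Visits 5, 6 and 7. Take erythema with intact epithelium, first seen at Visit 4 or 5, that is deeply disrupted at Visit 7. If it is followed as the same finding, the first-observation rule describes it as intact, although section 13.3 would call its later state severe. The AE table cannot show it, because it may not be entered on the AE form. The by-visit summaries in 14.6 and the shift tables in the synopsis point the other way, and the protocol does not say which governs.

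**4. Scale.** Sections 7.3 and 7.4 give at least 50 completers at 2:2:1, nominally 50 × 2/5 = 20, 20 and 50 × 1/5 = 10. One omitted woman is 1/20 = 5 percentage points in an active arm and 1/10 = 10 on placebo. The Treated Population may exceed the completers, which would make these steps slightly smaller.

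The documents give no rate of worsening. If a fraction p of women had a pre-insertion event that worsened (p is an assumption), the chance of at least one in an arm of n is 1 − (1 − p)^n:

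| Assumed p | n = 20 | n = 10 |
|---|---|---|
| 2% | 33% | 18% |
| 5% | 64% | 40% |
| 10% | 88% | 65% |
| 20% | 99% | 89% |

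This is the chance that the rule matters to someone in the arm. It is not the chance that an event is lost, which also requires that no new record is opened.

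**The case against.** The best reply on AEs is that section 13.1 already solves the problem. If a worsening under product is itself an AE, and all AEs must be recorded, then the worsening begins on or after insertion and section 14.6 includes it. That reading is reasonable and consistent with the single intensity per AE in section 13.3. It is not stated, however, and the same section classes anything with onset before first product use as pre-existing. The gap in dating remains.

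On colposcopy, the reply is that all observations are listed, genital endpoints are to be summarised by visit, the synopsis promises shift tables from baseline, and a colposcopist may diagnose a new ulceration rather than carry the earlier erythema forward. This also has force. It shows that progression may be visible elsewhere, but it leaves a specific first-observation rule beside general statements that conflict with it.

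Two further points limit the consequence. With about 50 women the listings can be read in full, and severe findings related to product go to the sponsor within 24 hours. In addition, at Visit 4 symptomatic infections lead to rescheduling or discontinuation, so fewer genital events are ongoing at insertion.

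A reader might infer that the plan systematically discards worsening toxicity, or that a known number of cases per arm will vanish. The documents support neither. The data are kept in listings, the AE outcome depends on site practice, and no rate of worsening is given.

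**Conclusion.** The inconsistency is real and lies in rules that the protocol itself fixes, not in detail left to an analysis plan. Followed literally, the onset-only definition can leave a worsened pre-insertion event out of the primary AE table, and the first-observation rule can show a progressing colposcopic finding at its mildest state. Both would understate progression. The conclusion rests on two conditions that the documents leave open: that a site updates an existing AE record instead of opening a new one, and that a changed colposcopic finding is followed as the same finding.

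The number of women affected cannot be estimated from the documents; the 5-point and 10-point steps are for scale only. The point is worth correcting in a descriptive trial whose primary objective is safety, but it does not undermine the design or lose the underlying data.

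**What to change.** In section 14.6, define a treatment-emergent AE as either of two things: an event with onset on or after insertion, or an event with earlier onset whose severity or frequency increases on or after insertion. In section 13, require the worsening to be entered as a new AE record, dated and graded at the worsening. The original record stays in the pre-insertion listing.

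For each non-iatrogenic colposcopic finding, add a by-arm summary of the worst post-insertion epithelial state (intact, superficial or deep disruption) against Visit 4 pre-insertion. Keep the first-observation description beside it, and state how both relate to the by-visit summaries and shift tables. Mirror the changes in the synopsis.

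The cost is a few sentences and one added recording instruction for sites. The instruction is needed because section 13.3 describes one intensity per AE, so the grade at worsening is not assured on the current forms. Repeat colposcopic observations are already planned and listed, so that summary needs no new examination. AE and finding counts may rise slightly.
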